### 2.5. Peanut oral immunotherapy

#### 2.5.1. Initial food escalation

Peanut OIT will be initiated 24 to 72 h after the first injection of either abatacept or placebo. The initial food escalation (IFE) will consist of an OFC of up to 300 mg of peanut protein. IFE doses (presented in Table 3) will be administered every 30 min up to the target maintenance dose of 300 mg or when stopping criteria are met.

**Table 3 T3:** Initial food escalation (IFE) up-dosing schedule.

**Dose administered (mg protein)**	**Cumulative dose (mg protein)**	**Observation time (minutes)**
1	1	30
3	4	30
10	14	30
30	44	30
100	144	30
300	444	120

Table 4 summarizes the OFC stopping rules, adapted from PRACTALL (39, 40), and details are presented in Supplementary Table 1. As a singularity in this protocol, subjective gastrointestinal symptoms, that are frequent during OFC, can be considered as possible conditions to stop OFC if they induce changes in behaviors. In case of subjective symptoms or objective signs that do not meet the stopping criteria, the investigator can delay the next dose (with a maximum of 45 min between doses) or repeat the same dose. A maximum of one dose can be repeated. In case of symptoms that do not appear in the PRACTALL guidance table, the investigator or medical staff will use their judgment to decide whether the OFC can be pursued or should be stopped. The investigator or medical staff will also decide how to effectively treat the reactions.

**Table 4 T4:** Stopping rules for oral food challenges.

**Category**	**Symptoms**	**Grade**			
I. Skin	A. Erythematous rash: % area involved
	B. Pruritus	0	1	2	3
	C. Urticaria	0	1	2	3
	D. Angioedema	0	1	2	3
II. Upper respiratory	A. Sneezing/Itching	0	1	2	3
	B. Nasal congestion	0	1	2	3
	C. Rhinorrhea	0	1	2	3
	D. Laryngeal	0	1	2	3
III. Lower respiratory	A. Wheezing	0	1	2	3
IV. Gastrointestinal	A. Subjective complaints	0	1	2	3
	B. Objective Complaints	0	1	2	3
V. Cardiovascular or neurologic		0	1	2	3

The challenge will be stopped when any symptom reaches the red level or when two symptoms from different categories reach a yellow level. Adapted from PRACTALL (39).

#### 2.5.2. Symptom-driven up-dosing

Subjects will begin daily home dosing with the highest tolerated dose from the IFE. The highest tolerated dose is defined as the highest dose that the investigator judges safe for the patient to take at home the following day. This is generally the dose immediately before the eliciting dose, but it can be a lower dose, depending on the severity of the reaction, as per the investigator's judgment.

Participants will return to the clinic every 2 weeks for a supervised escalation of their daily peanut dose. To be eligible for up-dosing, the participant must have taken his/her full dose at least 10 times in the last 14 days. If the participant does not meet this criterion, whether it was due to cofactor prevention, logistical issues (travels, family/work event), or forgetfulness, the up-dosing visit will be postponed until the criteria are met. Participants will be informed that compliance rates lower than 80% will lead to their exclusion from the OIT program for safety reasons.

Up-dosing will also be postponed in participants in whom it is contraindicated due to active illness or allergies.

Before up-dosing, the participant's dosing diary will be reviewed by the investigator to grade dose-related reactions using the revised CoFAR Grading Scale for Systemic Allergic Reactions (version 3.0) (41). By default, the first up-dosing will plan for a +100% increase in the currently taken dose. The planned percentage increase will then be adjusted based on dose tolerance at home, following the rules presented in Table 5. If the new dose is tolerated, the following visit will plan for the same percentage increase, to be adjusted the day of, according to the rules (Table 5).

**Table 5 T5:** Dose escalation management based on clinical tolerance.

**Home dosing symptoms during the last 2 weeks**	**Dose escalation management**
Persistent moderate (CoFAR Grade 2) or any severe (CoFAR Grade 3) or systemic reactions	No increase/next percent increase decreased by half on the following visit
Persistent mild (CoFAR Grade 1) or transient moderate (CoFAR Grade 2) local reactions	Decreased planned percent increase by half
Transient local symptoms (CoFAR Grade 1)	Proceed as planned
No or minimal symptoms^†^	Double planned percent increase

† Minimal symptoms refer to symptoms that the patient notice but does not describe as bothersome/not clinically significant, such as tingling of the tongue.

Participants who react to their dose escalation will not increase their daily dose and remain on the previously tolerated dose for another 2 weeks. The following up-dosing visit will plan for an escalation at half of the percentage increase of the failed escalation, to be adjusted based on the symptom diary. If escalation fails again, the following planned percentage increase will again be decreased by half at the subsequent visit and each following visit until the escalation is tolerated.

When the participant presents no symptoms at all to their daily dose, the up-dosing rules dictate doubling the percentage increase. However, if this would lead to an increase by a percentage up-dosing that had failed in the past, the participant is required to have two up-dosing visits with absolutely no symptoms in their diaries before proceeding to that new percentage increase, instead of just one.

Up-dosing visits will take place up to a maintenance dose of 300 mg, at which point the participant will remain on that daily dosage until the end of the study.

#### 2.5.3. Dose intake, cofactors, and dose adjustments at home

The participants will be provided with pre-weighted peanut flour doses and instructed to ingest their dose every day at around the same time. Participants will have 24 h access to research staff for support with home dosing and to guide interventions in case of adverse events. They will be trained in the recognition of anaphylaxis and cofactors that increase the risk of reactions when they are taking their dose (e.g., alcohol, exercise, and infections). They will be prescribed an epinephrine auto-injector and will be trained on its use.

Medication can be prescribed to prevent OIT-induced allergic symptoms with daily dosing, as per the investigator's discretion. This can include H1 and/or H2 anti-histamine, leukotriene receptor antagonists, proton-pump inhibitors, prostaglandin E1 analogs, mast cell stabilizers, and/or swallowed corticosteroids. These medications will be documented in the patient diary and concomitant medication log.

In the event of an identifiable cofactor (e.g., active viral infection), the OIT dose would be temporarily decreased by half. The participant would resume full dosing once the cofactor has been resolved. In the event of any systemic reaction or a moderate-to-severe local reaction at home, the OIT dose would be decreased by half until the following planned up-dosing visit.

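### Halving the dose after an early home reaction can postpone the up-dosing visit until Table 5's two-week lookback no longer shows the reaction

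*Protocol article*

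**What the plan says.** Three rules in the protocol article meet here.

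- **Halving (section 2.5.3).** After any systemic reaction, or a moderate-to-severe local one, at home, "the OIT dose would be decreased by half until the following planned up-dosing visit". The preceding rule halves the dose for a cofactor such as a viral infection, and there the text adds: "The participant would resume full dosing once the cofactor has been resolved".
- **Eligibility (section 2.5.2).** Visits are every two weeks. To be up-dosed, "the participant must have taken his/her full dose at least 10 times in the last 14 days"; otherwise "the up-dosing visit will be postponed until the criteria are met". Cofactor prevention is among the listed reasons for missing the criterion. Halving after a reaction is neither listed nor exempted.
- **Dose decision (section 2.5.2, Table 5).** The deciding column is headed "Home dosing symptoms during the last 2 weeks". Persistent moderate, severe or systemic reactions give "No increase/next percent increase decreased by half on the following visit". Persistent mild or transient moderate local reactions halve the planned percentage. No or minimal symptoms double it.

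For a participant with no symptoms, section 2.5.2 says that "the up-dosing rules dictate doubling the percentage increase". Its one brake applies "if this would lead to an increase by a percentage up-dosing that had failed in the past".

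**The concern.** The reactions that trigger halving are largely those that Table 5's two restraining rows are meant to catch. If the half doses make the participant ineligible, the visit moves. Because the lookback has a fixed length, the reaction can drop out of it before the visit is held. The rule that protects the participant at home would then switch off the matching rule at the next escalation.

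What is at stake is the size of the next dose step after a systemic or moderate-to-severe reaction, in participants selected for peanut-specific IgE above 50 kU/L. Two secondary outcomes in section 2.2 depend on these rules: time to the 300 mg maintenance dose and the mean cumulative function of dosing reactions. If staff resolve the gap case by case, escalation will not follow one rule.

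**Working it through.** The plan gives no figure to reproduce; this is a day count from its stated rules.

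**Inputs.** Visit interval 14 days, threshold 10 full doses in 14 days and lookback 14 days (section 2.5.2 and Table 5); halving until the planned visit (section 2.5.3).

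**Assumptions.** Number the 14 dosing days before the planned visit 1 to 14, with the visit on day 15 before that day's dose. Every dose is taken. One reaction occurs on day r at full dose D, half doses follow on days r+1 to 14, and D resumes on day 15. Half doses are not full doses. A visit on day V looks back over days V−14 to V−1.

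**Step 1, planned visit (V = 15).** Full doses in the window = r. For r = 10 to 14 the participant is eligible and the reaction is in view. For r = 1 to 9 the visit is postponed.

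**Step 2, later visits with the reaction still in view (V ≤ r + 14).** Full doses = (r − (V−14) + 1) + (V − 15) = r. Each new full dose pushes an old one out. For r = 5 and V = 18, the window is days 4 to 17 and the full doses fall on days 4, 5, 15, 16 and 17, which is 5. With r at most 9, the threshold is never met while the reaction is visible.

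**Step 3, reaction out of view (V ≥ r + 15).** Full doses = V − 15. Reaching 10 needs V = 25. The window is then days 11 to 24, with 4 half doses and 10 full ones. The delay is 25 − 15 = 10 days. Moving the visit by a whole two-week cycle (V = 29, window days 15 to 28) also loses the reaction.

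**Step 4, sensitivity to counting.** Ten variants were run. They differed in whether the clinic dose on the escalation day counts, whether the reaction-day dose counts as full, whether the visit day is in the window, when the full dose resumes, and whether halving ends on the planned date. With escalation on day 0:

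| Reaction on day | Halving ends on planned date (8 variants) | Halving runs to the actual visit (2 variants) |
|---|---|---|
| 1–8 | first eligible visit 9 to 11 days late, reaction out of view in all 8 | never eligible |
| 9 | either result, depending on the convention | either result |
| 10–13 | eligible on the planned date or one day later, reaction in view | eligible on the planned date, reaction in view |

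So days 1 to 8 are robust and day 9 is not.

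**Step 5, decision at the late visit.** On day 15 a systemic reaction would have given no increase and then half the percentage; a transient moderate local one would have halved the percentage. On day 25, if days 11 to 24 show no or minimal symptoms, Table 5 gives doubling; with transient Grade 1 symptoms, the plan proceeds unchanged. The brake in section 2.5.2 concerns a percentage that failed at escalation, not a home reaction.

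**Step 6, other postponements.** A visit postponed by k days for illness or travel has a window starting on day 1 + k, so symptoms on days 1 to k drop out. A one-week postponement loses days 1 to 7. This does not depend on how half doses are counted.

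**The case against.** The strongest reply is that a dose halved on instruction is the assigned dose, so taking it satisfies the 10-of-14 rule. That rule reads as an adherence check: its listed reasons are cofactor prevention, logistics and forgetfulness, and a compliance threshold follows. The reaction sentence in section 2.5.3 and the no-increase row in Table 5 both presuppose that the planned visit is held. On this reading the conflict through halving disappears. It is a fair reading, but no sentence states it, and the cofactor wording points the other way: a halved dose is set against full dosing, and cofactor prevention is a way to fail the criterion. An article may leave detail to the full protocol. Here, however, the threshold, the halving period and the lookback are all stated, and the difficulty lies in how they combine.

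The safeguards also count. The investigator reviews the diary, up-dosing is postponed for active illness or allergies, escalation is supervised, and staff can be reached at all hours. Any doubling on day 25 would follow ten full doses of D with no or minimal symptoms. The rules are the same in both blinded arms, and no between-arm bias is shown. All of this lowers the importance of the point. It does not bring the reaction back into the lookback.

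**Conclusion.** The point holds as a minor one. If half doses after a reaction are not full doses and full dosing resumes on the planned date, a reaction on about days 1 to 8 is outside Table 5's lookback at the first eligible visit, about 10 days late. The two restraining rows then do not act on it. Postponement for other reasons can cause the same loss. How often this would happen, and how often the later diary would be symptom-free, is unknown.

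A reader might infer more, but the documents do not support it:

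- **That the participant is locked out for good.** This requires halving to run to the visit actually held; section 2.5.3 says the planned one.
- **That a specific overdose follows, such as three times D instead of twice D.** This carries +100% forward after a reaction, although section 2.5.2 keeps the percentage only if the new dose is tolerated. It also takes D as the base on day 15, when the participant is on D/2. From D/2, the twofold comparator would be D. The text does not fix the difference.
- **That escalation speeds up.** The increase comes later; what is lost is the reduction in its percentage.
- **That the week-24 primary outcome is affected.** Nothing in the documents shows this.

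**What to change.** (a) Change the Table 5 header so that it covers symptoms since the last up-dosing visit. Alternatively, state that a reduction triggered by a reaction carries over to the next eligible visit.

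(b) In section 2.5.3, state that halving ends on the originally planned visit date, that the Table 5 decision is made then, and that the 10-of-14 rule still applies to any actual increase. Say also whether the percentage applies to the pre-reaction dose D or to D/2, and that one reaction reduces the percentage once.

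With both, the day-15 decision covers days 1 to 14, so every reaction day is in view. After a systemic reaction on days 1 to 9, the next regular visit is day 29. Its window, days 15 to 28, holds 14 full doses, so the participant is eligible 29 − 25 = 4 days later than in step 3, at a reduced percentage. For the halved-increase row, the earliest increase stays on day 25, with the smaller percentage.

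Simply exempting half doses from the count is less attractive, because it would allow an increase after as few as 1 to 9 full doses. The cost of the proposed change is a few sentences and somewhat slower escalation after an early-interval reaction.

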### 2.6. Oral tolerance testing phase

Oral tolerance will be assessed starting at week 36 to allow for a 4-month washout period after the last abatacept or placebo perfusion (Figure 3). Participants will undergo an OFC of up to 9,000 mg of peanut protein, corresponding to one serving of peanuts (1/4 cup), aimed at testing the extent of desensitization while on therapy. OFC-stopping rules are presented in Table 4 and Supplementary Table 1.

#### 2.6.1. 72 h SU testing (w38)

Participants who tolerate at least 300 mg of peanut protein on week 36 OFC will proceed to SU testing. They will be asked to continue daily dosing with 300 mg of peanut protein for 11 days, after which they will avoid peanuts for 72 h and then return to the clinic to repeat an OFC up to 9,000 mg of peanut protein.

#### 2.6.2. One-week SU testing (w40)

Participants who tolerate 300 mg of peanut protein on 72 h SU testing will resume daily dosing for 1 week and then avoid peanuts for a whole week, before returning to the clinic to repeat the OFC up to 9,000 mg peanut protein.

#### 2.6.3. Two-week SU testing (w43)

Participants who tolerate 300 mg of peanut protein on the 1-week SU testing will resume daily dosing for 1 week and then avoid peanuts for 2 weeks, before returning to the clinic to repeat the OFC up to 9,000 mg peanut protein (2w SU).

#### 2.6.4. Four-week SU testing (w48)

Participants who tolerate 300 mg of peanut protein on the 2-week SU testing will resume daily dosing for 1 week and then avoid peanuts for 4 weeks, before returning to the clinic for a final OFC up to 9,000 mg peanut protein on week 48.

At any time in the SU testing phase of the study, if a participant presents symptoms to the dose of 300 mg, they will resume peanut OIT and continue daily dosing with no further SU testing until the end of the study at week 48.

### 2.7. Prohibited prior and concomitant medication

At any time during the study, participants should not take any of the following treatments:

- Another investigational drug or approved therapy for investigational use;- Any biological immunomodulatory therapy or anti-tumor necrosis factor drug;- Any concomitant immunotherapy administered to any food;- Any aeroallergen or venom immunotherapy initiated or in the up-dosing phase during study participation;- Systemic steroids (intravenous, intramuscular, or oral dosing) for more than 7 days;- Beta-blocking agents.

Before OFCs, subjects will be asked to stop the use of antihistamines (72 h for short-acting and 5–7 days for long-acting) and theophylline (12 h).

Before skin prick testing, subjects will be asked to stop the use of antihistamines (72 h for short-acting and 7 days for long-acting).

### 2.8. Safety assessments

All adverse events (AEs) occurring during the study will be documented in the e-CRF. Concomitant illnesses, which existed before entry into the study, will not be considered AEs unless they worsen during the treatment period. All AEs, regardless of the source of identification (for example, physical examination, laboratory assessment, and reported by subject), will be documented, as well as their severity, seriousness, and causality. AEs attributed to food dosing during OIT will be treated as AEs of special interest (AESI). IgE-mediated reactions related to OIT dosing will be recorded separately from the AE log following the CoFAR grading system.

### 2.9. Statistical considerations

Based on observations from preclinical studies in mice, abatacept is expected to suppress the allergen-specific IgE surge induced by OIT. The relative change in specific/total IgE at 24 weeks will be compared between the two groups using Student's *t*-test. A 50% suppression was deemed clinically significant.

Based on the PALISADE trial (6), we expect the placebo group (OIT alone) to increase their specific IgE levels by 100% with a standard deviation of <30%. Based on this assumption, a sample size of 12 participants with a 1:1 randomization ratio would allow the detection of a 50% difference in the increase in sIgE, with an alpha risk of 0.05 and a power of 80%. A total sample size of 14 patients would allow to account for 15% of lost follow-up.

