### 2.2. Study outcomes

The primary outcome of the trial is the relative change from baseline in peanut-specific/total IgE ratio at the end of the treatment phase (week 24). The use of the specific/total IgE ratio aims to control for non-specific fluctuations in IgE production.

Secondary outcomes include the following:

The relative change in peanut-specific IgG4/IgE (sIgG4/sIgE) ratio from baseline to week 24.The absolute change in peanut sIgG4 from baseline to week 24.The maximum period of avoidance after which an OFC with 300 mg peanut protein is still tolerated.The mean cumulative function of food dosing allergic reactions.The highest tolerated dose on week 36 OFC.The time from the onset of OIT to the maintenance dose of 300 mg.The overall rate of adverse events (AEs).

Exploratory outcomes include the following:

a. Change in peanut atopy patch test from baseline to weeks 12, 24, and 48.b. Change in peanut skin test from baseline to weeks 12, 24, and 48.c. Relative change in peanut-specific/total IgE from baseline to weeks 2, 6, 12, 36, and 48.d. Relative change in peanut sIgG4/sIgE ratio from baseline to weeks 2, 6, 12, 36, and 48.e. Absolute change from baseline in peanut sIgG4 to weeks 2, 6, 12, 36, and 48.f. The highest tolerated dose on week 38 OFC [72 h SU].g. The highest tolerated dose on week 40 OFC [1-week SU].h. The highest tolerated dose on week 43 OFC [2-week SU].i. The highest tolerated dose on week 48 OFC [4-week SU].

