### 2.3. Selection of participants

The study aims to enroll 14 participants aged 14–50 years with serum peanut sIgE >50 kU/L. The inclusion and exclusion criteria are presented in Tables 1, 2, respectively. For female participants of child-bearing potential, a urine pregnancy test will be conducted on randomization day. Since asthma is an important concern when initiating OIT, a focus on uncontrolled asthma should be made. Criteria for uncontrolled asthma are as follows:

- History of two or more systemic corticosteroid courses within 6 months of screening or 1 course of systemic corticosteroids within 3 months of screening to treat asthma/wheezing;- One hospitalization or emergency department visit for asthma/wheezing within 6 months of screening;- Forced expiratory volume in 1 s (FEV1) <80% of predicted or FEV1/forced vital capacity (FVC) <75%, with or without controller medications;- Inhaled corticosteroid dosing of >500 mcg daily fluticasone (or equivalent).

**Table 1 T1:** Inclusion criteria.

1. Male or female participants 14–50 years old at screening visit.
2. History of IgE-mediated allergy to peanut protein.
3. Peanut-specific IgE level >50 kU/L.
4. Total IgE level <5,000 kU/L.
5. Willing to comply with all study requirements during participation in the study.
6. Signed informed consent and assent.

**Table 2 T2:** Exclusion criteria.

1. Previous adverse reactions to abatacept.
2. Known hypersensitivity to abatacept or any of its components.
3. Patients at risk of sepsis, such as immunocompromised or HIV positive.
4. Patient undergoing treatment with any other biologic agent.
5. Partly controlled or uncontrolled asthma, as defined by GINA 2020.
6. Unstable angina, significant arrhythmia, uncontrolled hypertension, chronic sinusitis, or other chronic or immunological diseases that, in the judgment of the investigator, might interfere with the evaluation, administration of the test drug, or pose additional risk to the subject (e.g., gastrointestinal or gastroesophageal disease, chronic infections, scleroderma, hepatic and gallbladder disease, and chronic non-allergic pulmonary disease).
7. Current users of oral, intramuscular, or intravenous corticosteroids, tricyclic antidepressants, or beta-blocker.
8. Concurrent/prior use of immunomodulatory therapy (within 6 months), including allergen-specific immunotherapy.
9. A diagnosis of eosinophilic esophagitis, eosinophilic colitis, or eosinophilic gastritis.
10. Pregnant or breastfeeding women.

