### 3.1. On the choice of proxy outcome

ATARI is intended as a proof-of-concept study and will likely not be powered to detect differences in clinical remission. Its primary aim is, therefore, to assess differences in a proxy outcome that would be associated with the development of clinical remission.

Based on the choice of proxy outcome, we observed from preclinical studies that abatacept suppresses the initial surge in sIgE with allergen exposure (32). This is assumed to be the consequence of the suppression of peanut sIgE-producing plasma cells and T-cell reactivation and is shown to correlate with the likelihood of clinical remission (9, 17, 18). If this key finding cannot be replicated in humans, it appears reasonable to assume that the likelihood of replicating the clinical effects would also be low.

One risk of using the surge in sIgE as a primary outcome in such a small sample is that we are highly vulnerable to random non-specific variations in total IgE productions, which could have a confounding effect and decrease power. In our own experience of longitudinal testing during peanut OIT or epicutaneous immunotherapy, spontaneous variations in sIgE, even large, are non-clinically significant when they parallel variations in total IgE, hence the choice to measure changes in the sIgE over total IgE ratio as the primary outcome.

Changes in the sIgG4/sIgE ratio are another paraclinical outcome that is often measured during OIT. Since IgG4 production follows the same non-specific expansion/contraction variations as IgE, it is generally a more reliable measure of longitudinal changes in OIT than sIgE alone. However, it is unclear how abatacept will affect sIgG4 production. Based on preclinical data, it is possible that it may suppress the rise in sIgG4, which would complicate interpretation. The sIgG4/sIgE ratio will, therefore, be treated as a secondary outcome.

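### The primary t-test on raw relative change is valid, but a log-ratio model adjusted for baseline would guard against chance imbalance in 14 participants at little cost

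*Protocol article*

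**What the plan says.** Section 2.2 defines the primary outcome as "the relative change from baseline in peanut-specific/total IgE ratio at the end of the treatment phase (week 24"). Section 2.9 states the test: "The relative change in specific/total IgE at 24 weeks will be compared between the two groups using" Student's t-test. Neither section mentions a transformation or a covariate.

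The sample size in section 2.9 assumes that the placebo arm will "increase their specific IgE levels by 100% with a standard deviation of <30" percent. It concludes that 12 participants, allocated equally to the two arms, "would allow the detection of a 50% difference in the increase in sIgE" at 80% power and a significance level of 0.05. The enrolled total is 14. The SD is stated for specific IgE, not for the ratio that is analysed.

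Section 2.4 specifies simple randomization, so baseline is balanced only by chance. Table 1 admits participants with "Peanut-specific IgE level >50 kU/L" and total IgE below 5,000 kU/L. The only adjustment mentioned anywhere is in section 3.4, for history of peanut exposure, in general terms. Section 3.2 says that the trial will inform the go/no-go decision on a larger trial.

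**The concern.** Dividing by baseline removes the influence of baseline only if the proportional change is unrelated to the starting level. Two things could break that.

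- **Regression to the mean.** A participant whose baseline ratio is high by chance tends to show a smaller relative rise. Randomization makes this equal between arms on average, but not in any one small trial.
- **Limited room to rise.** If specific and total IgE are on the same scale, the ratio cannot exceed 1, so a baseline ratio r0 allows a relative change of at most 1/r0 − 1. The entry limits allow ratios from just above 50/5,000 = 0.01, where this bound is very large. At r0 = 0.5 it is exactly the expected +100%.

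A raw percent change is also bounded below at −100% and has no common upper bound, so a longer right tail is plausible.

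At stake is precision, and the closeness of the observed difference to the truth when the arms happen to start apart. The validity of the test is not at stake.

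**Working it through.** **1. The plan's own figure.** Difference 50 points, SD 30, two-sided alpha 0.05 (sidedness is not stated), power 80%. The normal approximation gives n per arm = 2 × (1.96 + 0.84)² × (30/50)² = 2 × 7.85 × 0.36 = 5.65, so 6 per arm and N = 12. This reproduces. With the t distribution, power is 0.74 at 6 per arm and 0.82 at 7.

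**2. Chance imbalance.** In SD units, the difference in baseline means at 7 per arm has SD √(2/7) = 0.535. P(|difference| > 0.5) = P(|Z| > 0.5/0.535 = 0.935) = 0.35.

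**3. What an imbalance does.** Let r be the correlation of log change with log baseline. If log baseline and log follow-up have equal variance and correlation ρ, then r = −√((1 − ρ)/2), which is −0.50, −0.39 and −0.22 for ρ = 0.5, 0.7 and 0.9. In trials imbalanced by more than 0.5 SD, the mean imbalance is 0.535 × φ(0.935)/0.175 = 0.535 × 1.47 = 0.79 SD. The unadjusted difference in log change is then off by |r| × 0.79 × log-SD. At ρ = 0.7 the factor is 0.39 × 0.79 = 0.305:

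| log-SD of change | average error | share of the target, \|ln 0.75\| = 0.288 |
|---|---|---|
| 0.15 | 0.046 | 16% |
| 0.30 | 0.092 | 32% |
| 0.50 | 0.153 | 53% |

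Simulation at log-SD 0.5 agrees (0.15). In the same trials the adjusted model's average error is about 0.00. The plan's SD of 30% on a mean fold-change of 2.0 corresponds to log-SD √ln(1 + (0.30/2.0)²) = 0.149. The larger values are assumptions.

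**4. Skew and type I error.** For a lognormal fold-change at SD 30%, skewness is 0.45 (mean 2.0) and 0.61 (mean 1.5). It is 0.9 to 1.3 at SD 60% and 1.6 to 2.3 at SD 100%. Null rejection by the planned test was 0.043 to 0.053 in 40,000 trials per setting. A separate set of null runs gave 0.036 to 0.050.

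**5. Power at the plan's target.** +50% against +100% is a fold-change ratio of 1.5/2.0 = 0.75. Simulated power, 40,000 trials per cell; the ANCOVA columns run over r = 0, −0.3, −0.5, −0.7:

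| Setting | n/arm | planned t | log t | log ANCOVA |
|---|---|---|---|---|
| SD 30% in both arms | 6 | 0.74 | 0.75 | 0.70 / 0.74 / 0.81 / 0.93 |
| SD 30% in both arms | 7 | 0.82 | 0.83 | 0.79 / 0.82 / 0.88 / 0.97 |
| log-SD 0.29 in both arms | 6 | 0.32 | 0.34 | 0.31 / 0.33 / 0.38 / 0.53 |
| log-SD 0.29 in both arms | 7 | 0.38 | 0.39 | 0.36 / 0.39 / 0.46 / 0.61 |

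Separate runs at 7 per arm, ratio 0.75, for ρ = 0.5 / 0.7 / 0.9:

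- log-SD 0.3: planned 0.36 to 0.37, log t 0.38 to 0.39, ANCOVA 0.44 / 0.41 / 0.36.
- log-SD 0.15: planned 0.90 to 0.92, log t 0.91 to 0.92, ANCOVA 0.94 to 0.95 / 0.92 / 0.89 to 0.90.
- log-SD 0.5: planned 0.15, log t 0.17, ANCOVA 0.16 to 0.19.

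Logging alone adds about 1 to 3 points. The covariate helps clearly only when |r| exceeds about 0.3. At r = 0 and 6 per arm it costs about 4 points (0.74 to 0.70).

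**The case against.** The strongest reply is that the planned test is sound and the alternative buys little. Much of this stands.

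- **A reader might infer that the plan ignores baseline.** It does not. Relative change divides by baseline, which on the log scale is adjustment with the slope fixed at 1. Only an estimated slope is missing.
- **A reader might infer that adjustment always raises power.** It does not. The gain depends on a correlation that the document does not give, and near r = 0 there is a loss.
- **A reader might find a large gain by simulating a halved fold-change.** At log-SD 0.5 that gives 59% for the planned test and 75% for the adjusted model at ρ = 0.5. But halving a doubling (2.0 to 1.0) abolishes the surge. The plan targets 0.75, and at that target and log-SD every analysis has power below 0.20.
- **A reader might infer that one outlier can decide the go/no-go.** The null runs do not support this. The planned test stays at or slightly below its nominal level, because an extreme value inflates the pooled SD and mainly costs power.
- **Skew is not shown.** The document gives no distribution, and under its own SD the skew is mild. Section 3.1 does concede "One risk of using the surge in sIgE as a primary outcome in such a small sample", but the risk named there is non-specific variation in total IgE, which the ratio is meant to address. It is not about baseline adjustment.
- **The target changes scale.** A log model estimates a ratio of geometric means, whereas section 2.9 defines the important effect as a difference in percent increase.

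The reply does not remove the imbalance argument. Randomization protects the error rate over repeated trials, but the one trial that is run may start unbalanced. Nor does the SD below 30% settle the matter, since it is stated for specific IgE and not for the ratio.

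**Conclusion.** The concern holds as an inexpensive improvement in efficiency and robustness, not as an error in the test. The unadjusted analysis leaves a trial of 14 exposed to a baseline difference above 0.5 SD with probability of about 35%. If ρ is 0.7, such imbalances shift the log estimate by about 16% of the target effect at the plan's SD, and by more if the ratio varies more.

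The expected power difference at the plan's target runs from about +8 to 0 points at log-SD 0.3 and from about +5 to −3 points at log-SD 0.15, as ρ goes from 0.5 to 0.9. These figures assume lognormal fold-changes. The log-SD and the correlations are assumptions, because the document supplies neither for the ratio. The point does not extend to the sIgG4/sIgE secondary outcome, for which the document names no test.

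**What to change.** Amend section 2.9 before unblinding. Make the primary analysis a linear model of log(sIgE/total IgE) at week 24 on treatment and baseline log(sIgE/total IgE), reported as a ratio of geometric mean fold-changes with a 95% confidence interval. Restate the 50% suppression target on that scale as 1.5/2.0 = 0.75, noting that the ratios of geometric and arithmetic means agree only if the log-SD is the same in both arms. Keep the Student's t-test on relative change as a sensitivity analysis.

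The change needs no new data or participants. It costs one degree of freedom (10 to 9 at 6 per arm), with a loss of about 4 points of power at that size if the change turns out to be unrelated to baseline. It also moves the effect measure from arithmetic to geometric mean change, so the effect that counts for the go/no-go must be stated on the new scale beforehand.
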